## Abstract

**Background:**

Environmental Enteropathy (EE), characterized by alterations in intestinal structure, function, and immune activation, is believed to be an important contributor to childhood undernutrition and its associated morbidities, including stunting. Half of all global deaths in children < 5 years are attributable to under-nutrition, making the study of EE an area of critical priority.

**Methods:**

Community based intervention study, divided into two sub-studies, 1) Longitudinal analyses and 2) Biopsy studies for identification of EE features via omics analyses. Birth cohorts in Matiari, Pakistan established: moderately or severely malnourished (weight for height Z score (WHZ) < − 2) children, and well-nourished (WHZ > 0) children. Blood, urine, and fecal samples, for evaluation of potential biomarkers, will be collected at various time points from all participants (longitudinal analyses). Participants will receive appropriate educational and nutritional interventions; non-responders will undergo further evaluation to determine eligibility for further workup, including upper gastrointestinal endoscopy. Histopathological changes in duodenal biopsies will be compared with duodenal biopsies obtained from USA controls who have celiac disease, Crohn’s disease, or who were found to have normal histopathology. RNA-Seq will be employed to characterize mucosal gene expression across groups. Duodenal biopsies, luminal aspirates from the duodenum, and fecal samples will be analyzed to define microbial community composition (omic analyses). The relationship between histopathology, mucosal gene expression, and community configuration will be assessed using a variety of bioinformatic tools to gain better understanding of disease pathogenesis and to identify mechanism-based biomarkers. Ethical review committees at all collaborating institutions have approved this study. All results will be made available to the scientific community.

**Discussion:**

Operational and ethical constraints for safely obtaining intestinal biopsies from children in resource-poor settings have led to a paucity of human tissue-based investigations to understand and reverse EE in vulnerable populations. Furthermore, EE biomarkers have rarely been correlated with gold standard histopathological confirmation. The Study of Environmental Enteropathy and Malnutrition (SEEM) is designed to better understand the pathophysiology, predictors, biomarkers, and potential management strategies of EE to inform strategies to eradicate this debilitating pathology and accelerate progress towards the 2030 Sustainable Development Goals.

**Trial registration:**

Retrospectively registered; clinicaltrials.gov ID NCT03588013.

**Electronic supplementary material:**

The online version of this article (10.1186/s12887-019-1564-x) contains supplementary material, which is available to authorized users.

## Background

Environmental Enteropathy (EE), an acquired small intestinal condition, is a consequence of the continuous burden of immune stimulation by fecal-oral exposure to enteropathogens leading to a persistent acute phase response and chronic inflammation [1, 2]. First described in the 1960s and 1970s [3–5] in studies from Asia, Africa and Central America, morphological changes or functional signs of EE were identified in a high proportion of apparently healthy adults and children [6–9]. EE can be characterized histologically by villus shortening, crypt hyperplasia and resultant decrease in the surface area of mature absorptive intestinal epithelial cells which leads to macro- and micronutrient malabsorption [1, 10]. Concomitant intestinal leakage or permeability can be estimated by dual sugar absorption tests which have been widely used as a surrogate for biopsy based diagnoses [11, 12]. Permeability can lead to translocation of microbes or microbial products which along with the intestinal inflammatory nidus, can produce systemic immune activation. This chronic inflammation along with malabsorption are postulated to be the mechanisms through which EE contributes to undernutrition, especially linear growth faltering [13, 14]. Undernutrition is implicated in 45% of the 5 million annual deaths in children under 5 years of age [15] and linear growth failure (stunting, length-for-age Z score < − 2) is a common manifestation of undernutrition, afflicting ~ 155 million under-fives worldwide [16]. Stunting serves as a clinical marker for lifelong impairments in physical, neurocognitive, vaccine immunological response, and socioeconomic potential [17–20]. Our current understanding of EE is limited, in large part, because the tissue affected, the gastrointestinal tract of malnourished children, has been difficult to obtain in resource limited settings. Further, a comprehensive approach incorporating longitudinal surveillance of affected children to identify the impact of EE from other co-morbid conditions is needed to fully capture risk factors for EE. Therefore, we propose a comprehensive study approach which combines longitudinal surveillance of children from birth until 2 years of age, capturing known and postulated risk factors of EE and applying the most advanced tools for the analysis of the intestinal tissue samples. The Study of Environmental Enteropathy and Malnutrition in Pakistan (SEEM Pakistan), is a follow up to our phase 1 study titled ‘Identification of Novel Biomarkers for Environmental Enteropathy in Children Using an Evidence Based Approach’ [14, 21–23], in which we have studied patterns of malnutrition and prevention in a cohort of children in Matiari, Pakistan and looked at potential biomarkers of EE and at the ethical feasibilities of conducting biopsies in a low- and middle income country (LMIC) setting. Building on our experience from this study and related works [14, 21–23], our SEEM Pakistan study is designed to better understand the pathophysiology, predictors, biomarkers, and potential management strategies of EE. This report describes the SEEM Pakistan study design, including the materials that are being collected along with proposed analysis including use of machine learning methods.

## Methods

SEEM Pakistan is a multi-institutional collaboration between the Aga Khan University Hospital (AKUH), Pakistan, University of Virginia (UVa), Cincinnati Children’s Hospital Medical Center (CCHMC) and Washington University in St. Louis (WUSTL) in the USA, with funding by the Bill and Melinda Gates Foundation (2016 through 2019). Enrollment has been completed and a cohort of 400 children has been established (350 malnourished children and 50 well-nourished healthy controls).

### Objectives

This study aims to (i) establish a cohort of 350 malnourished and 50 well-nourished children in Matiari, Pakistan aged zero to 6 months; (ii) assemble serum, fecal, and urine samples for assessment as biomarkers of EE; (iii) provide educational and nutritional interventions according to the level of malnutrition of the child; (iv) evaluate the subset of malnourished children who fail to respond to educational and nutritional interventions by upper gastrointestinal (UGI) endoscopy to identify treatable causes of malnutrition; (v) use the UGI biopsy specimens obtained for detailed assessment of histopathology, gene expression and immune profiling to better characterize the pathophysiology of EE, validate current candidate biomarkers, and discover novel biomarker candidates. Importantly, this study provides a unique opportunity to examine whether there are identifiable relationships between histologically-diagnosed EE and the configuration of the proximal small intestinal and fecal microbiota. Moreover, preclinical tests of causality will be performed by transplanting bacterial communities recovered from children with EE into gnotobiotic mice and assessing the degree to which these communities transmit histopathologic, transcriptional, proteomic and immunologic features of the children’s gut barrier dysfunction phenotypes. With these goals in mind, SEEM is comprised of two primary sub-studies: 1) Longitudinal analyses of growth in birth cohort members and 2) Correlating ‘omic phenotyping with biopsy analysis, including correlating gut microbial community features with features of duodenal mucosal gene expression profile and immune phenotypes. Table 1 further describes these two primary sub-studies, including objectives covered under each study, their hypotheses, and the patient population selected for each objective.

**Table 1 Tab1:**
[figure not shown]
Objectives, hypotheses, and study population of the primary SEEM sub-studies

### Patient and public involvement

Our enrollment population consists of children under the age of 2 years. Therefore, not the patients themselves but their parents were indirectly involved in certain aspects of SEEM’s study design. Our field study staff has ongoing routine feedback and evaluation with the parents of the patients, and the current design was evolved based upon our and patient/parental experience from our phase 1 EE study [14]. For example, due to a parent-reported increase in their child’s diarrhea after consumption ready-to-use therapeutic food, we replaced it with a locally made supplement (Acha Mum) in the current study. Furthermore, feedback from the parents is encouraged, and all issues and comments are communicated to the study team during weekly community meetings. We plan to disseminate results to each participant/parent at the Matiari field-site office at the end of the study.

### Study settings and participants

The basic framework for the SEEM Pakistan study is described in Figs. 1 and 2. The Department of Paediatrics and Child Health at AKUH has an established field site at Matiari, Pakistan, which is a rural district about 3 hours drive north of Karachi, Pakistan. We anticipated enrolling 350 children from ages 0 to 6 months with weight for height Z score (WHZ) < − 2 at the time of enrollment. We also anticipated enrolling 50 children of the same age with healthy ponderal and linear anthropometric assessments based on consistent WHZ > 0 and height for age Z score (HAZ) > − 1 on two consecutive visits between 3 to 6 months, to serve as healthy controls. Administration of routine rotavirus vaccine will be facilitated as a part of our study, and other Expanded Program on Immunizations (EPI) vaccines will also be facilitated as part of other ongoing research activities.

**Fig. 1 Fig1:**
[figure not shown]
Conceptual framework for hypothesis testing in SEEM. The severity of clinical phenotypes in Matiari children with wasting and suboptimal response to nutritional rehabilitation will highly correlate with the histopathological appearance of duodenal biopsies; duodenal and fecal dysbiosis; perturbation of duodenal gene expression profiles; systemic biochemical profiles; and children’s genotypes. The image in the top right panel demonstrates the histological changes observed in the small intestine as environmental enteropathy progresses. Note: *L:R* lactulose:rhamnose ratio, *EE* environmental enteropathy, *GI* gastrointestinal, *HLA* Human Leukocyte Antigen

**Fig. 2 Fig2:**
[figure not shown]
SEEM Data Collection Process. Note: *CHW* community health workers, *UGI* upper GI, *WHZ* weight for height Z score

Blood, urine, and fecal samples will be collected from all participants between 3 and 6, and at 9 months of age as well as at the time of endoscopy for those who undergo the procedure (Table 2). Lastly, feces will be collected from participants eligible for nutritional intervention at 10 months of age (pre-intervention) and then again at around 14 months of age (post-intervention). Duodenal aspirates will also be collected at the time of endoscopy; a dry aspirate (pre-saline lavage) as well as a wet aspirate (post-saline lavage) will be attempted.

**Table 2 Tab2:**
[figure not shown]
Description of sample collection

After enrollment, the parents/caregivers of all participants will undergo a series of rehabilitative interventions to improve the child’s nutritional status. Those participants who remain moderately or severely malnourished (WHZ < − 2 or < − 3, respectively) despite interventions will then be eligible for medical evaluation to assess if s/he merits further clinical workup of malnutrition, including UGI endoscopy, to identify a secondary cause. Those who qualify for UGI endoscopy will also undergo a biopsy workup as described in Table 3.

**Table 3 Tab3:**
[figure not shown]
Plan of biopsy work up on children selected for UGI endoscopy

Because UGI endoscopies are rarely performed in children under 2 in Pakistan and due to ethical and cultural considerations, it is not possible to obtain duodenal biopsies from national healthy children that could serve as a control in our analysis. This is one of the major limitations of our study and as the results from Campbell et al. [10] support the utility of healthy age-matched children from high-income countries for identifying key gut pathogenic pathways in low-income settings, we are proposing to use age-matched controls from the United States for comparison.

Therefore, we plan to enroll 3 different control groups, all comprising of children under the age of 11 years, with a preference to enroll children under the age of 5 years. Our first control group will comprise of 30 healthy children, who will undergo endoscopy at CCHMC as part of a diagnostic workup for digestive symptoms, but whose biopsies and diagnoses are not supportive of eosinophilic esophagitis, celiac disease, or inflammatory bowel disease, and who were not treated with antibiotics ≤4 weeks prior to endoscopy.

As EE and celiac disease share some shared histopathological features [24, 25], we will focus on celiac disease as an enteropathy control group. We plan to enroll 30 children with newly diagnosed celiac disease per endoscopy at CCHMC to assess the extent to which gene signatures and associated biologic pathways for children with celiac disease or EE overlap or differ. Lastly, while we recognize that duodenal and ileal histopathology in the majority of Crohn’s cases differ from celiac disease and EE, the differentially expressed ileal gene signature in Crohn’s patients bears remarkable similarities to individual gene expression patterns reported for EE [10, 26], i.e. induction of IFN_γ_, REG1B. Therefore, our third control group will be 30 children with newly diagnosed Crohn’s disease per endoscopy at CCHMC.

### Sample size

Participants will be recruited from our prospective cohort. Based on our phase 1 cohort [14], we anticipated that the cohort of 50 SEEM patients, with duodenal samples collected by endoscopy, will include at least 20 without a single identified treatable infection, i.e. identified *Giardia* or *H. pylori* infection*.* The primary endpoint guiding our sample size estimate will be the anticipated differences in duodenal IFN_γ_ and APOA1 gene expression between subjects with EE and healthy controls. We anticipate that induction of IFN_γ_ gene expression will be associated with a reduction in APOA1 gene expression as per a recent study on Crohn’s disease [27] and that of Bragde et al. on celiac disease [28]. In the Crohn’s study, the mean (SD) Reads Per Kilobase per Million Mapped reads (RPKM) IFN_γ_ gene expression at diagnosis was equal to 1.86(2.7) in patients with Crohn’s, and 0.33(0.38) in healthy controls. The mean (SD) RPKM APOA1 gene expression at diagnosis was 927(1469) in patients with Crohn’s, and 3012(3080) in healthy controls. We anticipate similar differences between EE and healthy controls in our study. Based on these results, 30 healthy controls and 25 EE subjects without a specific treatable infection will provide 90% power to detect such a difference with α = 0.05. The secondary endpoint will be to perform an undirected analyses to capture the overall gene and signatures that are different between described groups. Based on previously published data for RNA-Seq samples size estimation [29], if we estimate a coefficient of variation of counts of 0.4 as was observed in 90% of the genes in a range of human studies, alpha of 0.05 and power of 0.8, a sample size of 20 per group will be needed.

### Educational and nutritional interventions, and steps following failure

Upon enrollment at age < 6 months, infants will be started in a 4-week home delivered educational program that will focus on breast feeding and complimentary feeding. Counseling will be performed by the study staff using standardized teaching materials. Compliance to the instruction will be recorded during weekly home visits.

If the WHZ remains < − 2 by 9 months of age despite the initial educational counseling, s/he will be enrolled in the second phase of nutritional and educational intervention. Families will be shown a 10 min educational video that details the best practices with respect to complimentary feeding best practices on a fortnightly basis, and compliance to the instructions will be recorded during the weekly home visits. If the child remains at WHZ < − 2, s/he will undergo the third phase of rehabilitation management according to Pakistan’s Community Management of Acute Malnutrition protocol [30]. This will include provision of Acha Mum for the treatment of moderate and severe acute malnutrition to the child at home with close follow up. Utilization of the food supplement will be monitored closely by weekly home visits.

For those children who fail to respond to nutritional rehabilitation and in whom no apparent cause of malnutrition can be identified after basic laboratory workup, we will conduct a more thorough investigation to identify the cause of undernutrition. It is important to note that this nutritional rehabilitation program is immensely supervised, with study staff allowed to visit homes more than once a week to ensure compliance if required. Additionally, our Phase 1 study had a 90.5% compliance for nutritional intervention, and we will therefore be able to identify which children fail to respond to rehabilitation due to biological reasons vs the unlikely event of failing due to a lack of compliance. If the child remains at WHZ < − 2 despite all the above interventions, then s/he will undergo medical evaluation (including a core standardized laboratory panel which includes celiac screening, complete blood count, complete metabolic panel, international normalized ratio, erythrocyte sedimentation rate, and C-reactive protein, additionally, the pediatric gastroenterologist will not be limited to this panel and may order any additional tests as clinically indicated) to assess if there is a clinical indication for further workup to identify a secondary cause of the malnutrition, including UGI endoscopy at AKUH. Diagnostic evaluation, including the UGI endoscopy, will be used to guide further management. For example, dietary management of celiac disease counseling (i.e. initiation of gluten free diet [31]), will be provided to the families of affected children in the local language, and identified infections will be treated according to the standard of care (as was performed in our Phase 1 study for n = 1 child diagnosed with celiac disease [14]). Follow-up will be continued to facilitate treatment and ensure the best possible outcomes depending on the pathology identified.

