### Histopathologic, immunohistochemistry and transcriptomic work up of biopsy specimens

We hypothesize biopsies from children whose endoscopic workup does not reveal a clear malabsorptive pathology, such as celiac disease, will likely demonstrate advanced features of EE. Previous studies suggest at least two factors contribute to EE: (i) chronic T-cell mediated intestinal damage and (ii) perturbations in microbial community structure/function [13, 48]. Recognizing that our sample will be restricted to children whose wasting (WHZ ≤ − 2) is refractory to nutritional intervention, we will comprehensively assess biopsy specimens to better understand the pathology of the proximal small intestinal mucosa in EE.

One such previous attempt utilizing duodenal biopsies compared malnourished children in Gambia with healthy UK age-matched children to better understand the pathogenesis underlying this disorder [10]. This study was, however, restricted to morphometric and targeted immunohistochemical analyses for immune cell markers, and did not investigate gene expression associated with the absorptive epithelial layer more broadly. The authors concluded that cell-mediated Th1 response might impair mechanisms of oral tolerance and drive progressive growth failure despite intensive nutritional intervention [10]. Therefore, we propose to supplement routine clinical histologic morphometric analyses with (i) targeted staining to characterize immune cells and the epithelial layer (working with the UVa Biorepository and Tissue Research Facility (BTRF) we have recently established a protocol for triple color immunohistochemical staining), (ii) RNA-Seq analyses to capture a more inclusive EE gut gene expression signature, (iii) gut biopsy DNA-based 16S rDNA characterization of the biopsy-adherent bacterial communities, and (iv) perform microbe:gene association studies (Fig. 3). We hope that these data will provide new insights into both disease pathogenesis and treatment, as well as gut-derived circulating biomarkers for disease severity, which may be assayed in future studies using the banked sera from the larger 400 patient SEEM cohort.

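### An average Phase 1 compliance of 90.5% does not show that non-compliance is an unlikely cause of failure among children selected because they failed, and no stated rule uses each child's own utilisation

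*Protocol article*

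**What the plan says.** All of this is in the protocol article.

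- *Educational and nutritional interventions, and steps following failure* gives two grounds for setting non-compliance aside. The first is intensive supervision, with "study staff allowed to visit homes more than once a week to ensure compliance if required". The second is that "our Phase 1 study had a 90.5% compliance for nutritional intervention". From these it concludes "we will therefore be able to identify which children fail to respond to rehabilitation due to biological reasons vs the unlikely event of failing" for want of compliance.
- The same section provides the monitoring. Compliance with the educational instructions is recorded at weekly visits in the first two phases. For the third phase, "Utilization of the food supplement will be monitored closely by weekly home visits".
- Entry to the diagnostic step depends on WHZ: a child still below −2 "despite all the above interventions, then s/he will undergo medical evaluation". Endoscopy then needs a clinical indication. Neither step states a compliance condition.
- *Patient and public involvement* reports that parents saw more diarrhea "after consumption ready-to-use therapeutic food", and that "we replaced it with a locally made supplement (Acha Mum) in the current study".
- *Histopathologic, immunohistochemistry and transcriptomic work up of biopsy specimens* says "our sample will be restricted to children whose wasting" is refractory to nutritional intervention.
- *Data analysis plan* names factors for subdividing the EE group (identified infection, CRP, histologic severity, rotavirus response, weight and height outcomes) and for adjustment (age, gender, body mass index and, in some analyses, genetic variants). Supplement utilisation is not among them.

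**The concern.** The 90.5% is an average over treated children. The claim it supports is about a different group: children who stayed wasted after treatment. If feeding works at all, children who take less of the supplement fail more often, so selection on failure raises their share. A low overall rate of non-compliance therefore does not carry over to the selected group.

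The figure is also weak evidence for this study. The article does not say whether it counts children, doses or intake, and it appears to come from the period before the supplement was changed.

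Most exposed are the analyses that use non-response itself as a label. The *Lactose/Rhamnose (L:R) test* section asks whether failure to respond is associated with altered permeability. Failures due to low intake would tend to dilute that association. The same applies to biomarker comparisons by response and to describing the biopsied group as refractory. The *Discussion* accepts that EE is presumed where no gut infection or other GI pathology is found, so a low-intake child with no such finding would be counted as presumed EE.

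**Working it through.** **The plan's own figure.** The 90.5% has no numerator, denominator or definition, so it cannot be reproduced. Two assumptions are needed to use it: that it is a share of children, and that it carries over to Acha Mum. Then the non-compliant share is q = 1 − 0.905 = 0.095.

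**Formula.** Let fn and fc be the failure rates in non-compliers and compliers, and RR = fn/fc. By Bayes' rule,

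share of non-compliers among failures = q·fn / (q·fn + (1 − q)·fc) = 0.095·RR / (0.095·RR + 0.905).

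The documents give neither fn nor fc, so a range is shown. Counts are per 50 children, the planned endoscopy cohort in *Sample size*, as if endoscopy followed failure without further filtering.

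| RR | Calculation | Share | Of 50 |
|---|---|---|---|
| 1 | 0.095 / 1.000 | 9.5% | 4.8 |
| 1.5 | 0.1425 / 1.0475 | 13.6% | 6.8 |
| 2 | 0.190 / 1.095 | 17.4% | 8.7 |
| 3 | 0.285 / 1.190 | 23.9% | 12.0 |
| 5 | 0.475 / 1.380 | 34.4% | 17.2 |

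**When enrichment is small.** Suppose every non-complier fails (fn = 1):

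- fc = 0.9: 0.095 / (0.095 + 0.8145) = 10.4%
- fc = 0.7: 0.095 / (0.095 + 0.6335) = 13.0%
- fc = 0.5: 0.095 / (0.095 + 0.4525) = 17.4%
- fc = 0.3: 0.095 / (0.095 + 0.2715) = 25.9%

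So the share stays near 10% only if almost all compliers also fail, and it grows as feeding works better.

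**What dilution could mean for a non-response contrast.** Suppose, as a further assumption, that failures due to low intake have the same mean permeability as responders. A true difference D between refractory children and responders is then observed as (1 − share)·D. At 13.6% that is 0.864·D; at 34.4% it is 0.656·D. If low intake itself alters permeability, the effect differs.

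**The case against.** The strongest reply is that 90.5% is only the second ground. The first is close supervision, and the sentence states an intention to tell the two kinds of failure apart. Weekly visits could supply the child-level data to do so, and a medical evaluation with a clinical indication comes before any endoscopy. This stands in part: the means of separation exist. But neither the entry criterion, nor the refractory label, nor the listed analysis factors uses them, and the word unlikely still leans on an average that cannot support it.

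A utilisation cut-off could also sit in a full protocol or analysis plan that is not shown, and the confounder assessment by causal pathway in *Data analysis plan* might bring utilisation in. That is fair, and the absence of a cut-off is not itself the fault. The fault is the stated inference, together with a label that relies on it.

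Four stronger readings may tempt a reader; the documents support none of them.

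- *A large part of the biopsied group was unfed.* Non-compliance may be partial, and the 90.5% may describe intake rather than children. If all 350 malnourished children reached the feeding phase and only 50 failed, the arithmetic ceiling would be 350 × 0.095 / 50 = 66.5%. The number reaching that phase is not given, and children who do reach it have already stayed below WHZ −2 through two phases, so high failure among compliers is plausible.
- *The new supplement lowers compliance.* The change was made for tolerability, so compliance could be higher. The article also does not tie the 90.5% to a product; that link is inferred.
- *The team assumes that every failure is biological.* The text says it will distinguish the two.
- *The main gene-expression comparison is undermined.* It sets EE subjects without a treatable infection against US controls, and EE severity is graded by histology, not by intake. Nothing shows that low-intake children have control-like expression.

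**Conclusion.** The inference from 90.5% does not hold for children selected on non-response and should be removed. Non-compliers would make up about 14% to 34% of failures for relative failure risks of 1.5 to 5, or roughly 7 to 17 of 50 biopsied children if endoscopy followed failure directly. The share would be near 10% if almost all compliers also fail. This rests on reading 90.5% as a share of children, carrying it over to Acha Mum, and assumed failure rates. The direction of enrichment is firm whenever non-compliers fail more often than compliers; its size is not established. The consequence falls mainly on analyses and descriptions that use the non-response label, not on histologic grading of EE. It is worth correcting because the remedy is cheap.

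**What to change.** 1. Delete the inference from the Phase 1 figure. Keep the description of supervision and of the intention to separate the two kinds of failure.
2. For analysis only, classify each non-responder as adequate or low utilisation from that child's weekly Acha Mum monitoring. Fix the cut-off before biopsy and L:R data are seen. Enrollment is already complete, so if some results exist, someone without access to them should set it.
3. Report the distribution of utilisation in the biopsied group.
4. Repeat the analyses that rely on non-response (L:R, biomarkers, the description of the biopsied group as refractory) restricted to or stratified by adequate utilisation. Keep the all-children analysis alongside.

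The cost is a change of wording, one classification variable and some repeated analyses. It assumes that the weekly monitoring leaves a usable record per child; the article says utilisation is monitored but uses the word recorded only for compliance with instructions. The restricted group will be somewhat smaller and its estimates less precise. The clinical route to evaluation and endoscopy is unchanged.
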